### Food diary protocol

The weighed food diary will commence on the participants day of surgery (day zero) and will conclude at post-operative day three inclusive. The weighed food diary will consist of the researcher using an electronic digital kitchen scale with a weight graduation of 1 g (AccuWeight 201, maximum weight 5 kg) to weigh all items served to the participant before and after their mealtime. The researcher will not serve any food directly, with plates or bowls placed directly on the digital scale and recorded by the researcher. Should a food be packaged with a specified weight – for example a yoghurt, said weight on the packaging will be recorded. Fluid intake will be recorded according to each mealtime (e.g. a cup of tea or fruit juice) and the researcher will liaise with the ward staff to log how many jugs of water the participant has consumed daily, and if this has been accompanied with other items such as cordial. A baseline measurement of water jugs, cups and beakers will be taken prior to the study commencing.

The researcher will not be present nor disrupt the participant during their meal, and after their food tray has been retrieved, the researcher will weigh the plate if it is a complete meal (e.g. lasagne), or, if it is a multiple item meal (e.g. meat, potatoes and vegetables), the researcher will weigh the leftover components individually to ensure the validity of the weighed food method and to achieve the highest degree of accuracy possible. After mealtime has concluded, the researcher will briefly ask the participant if they have had any snacks between their meals. Any observed assistance with meals (such as a family member) will be confirmed with ward staff. Additionally, as part of the specific NOF pathway in place, all hip fracture patients regardless of MUST screening assessment are required to consume two oral nutritional supplements (Nutricia™ Fortisip Compact or Fortisip Compact Protein) daily. The researcher will liaise with the ward staff regarding consumption and additionally will record the amount consumed. Data will also be collected regarding the times of meals and the ratio of staff to patients on the ward during each mealtime.

The researcher will liaise daily with the participant's named nurse regarding complications that may develop post-operatively during the study period, such as delirium, pressure ulcers, infection and venous thromboembolism.

### Adverse events

Should a participant experience an adverse event during the study, such as a stroke, myocardial infarction, major haemorrhage requiring a blood transfusion, the participant will be removed from the study, which was agreed after consultation with the study site research department. If a participant is removed from the study due to an adverse event, any data collected up until that point will be kept in the study and anonymous and an adverse events record made. The participants’ end point in the study will be when LOS and discharge destination data is obtained by the researcher.

### Outcome measures

#### Baseline characteristics

Table 1 outlines the range of data that will be collected such as sociodemographic, nutritional status and medical history and will be analysed in Microsoft Excel.

#### Dietary intake

We will analyse if dietary intake is sufficient to meet estimated REE requirements and explore the effect of dietary intake as a predictor of LOS and post-operative complications. Current guidelines will be used to calculate REE, and we will use a factor of 23 kcal/kg actual body weight per day for ‘surgical fixation of a hip fracture’ according to the supporting evidence-based recommendations specified in the guidelines (Todorovic and Mafrici, 2018). Using macronutrient data for hospital meals provided by the trust, consumption and waste per meal will be calculated according to energy (kJ/kcal), protein, carbohydrates, fats and fibre. For any snacks consumed or foods not listed by the hospital, Nutritics v6.00 software will be used for macronutrient data (Nutritics, 2024).

#### Covariates

LOS data (measured in days) will be obtained from the participants medical records, and the occurrence of post-operative complications will be checked daily with the gatekeeper per participant.

The consent form for participants with capacity and the Consultee Form for participants without capacity were approved by the NHS Ethics Committee. A registered dietitian that is not linked to the study site (CJ) reviewed the study protocol, weighed food diary chart and outcome measures.

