## Methods

### Design

The design is a prospective study using a convenience sampling method. The novelty of this study is grounded in the approach of a post-operative weighed food diary. Rather than participant recall, ward staff recall or asking ward staff to weigh food (which was not feasible due to ward staff workload), the researcher will weigh and record the participants dietary intake which will therefore increase the accuracy of the data obtained.

Using this design and methodological approach may offset potential refusal to participate in the study as there is no foreseeable risks to the participant nor burden which could potentially lower attrition risks. The design of this study is aimed at exploring biopsychosocial factors associated with older adult hip fracture patients’ outcomes in relation to LOS and post-operative complications. In particular, the inclusion of participants that lack capacity and/or in the presence of comorbidity could provide crucial insight to a subgroup of an at-risk population that has been previously excluded. The study will be conducted in one phase of 4 weeks. Participants enrolled on the study will not be able to obtain their data after the study has been completed as they will be anonymised and assigned a unique reference number after LOS and discharge destination data has been obtained. With no second phase of the study, participants’ identifiable data will not be retained for future research purposes.

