### Enrolment procedure

With agreement, the researcher will discuss the study with the participant and family or carers if present and provide the participant with a patient information sheet (PIS) and consent form to read in full. After 1 hour, the researcher will return and obtain informed consent. The lead researcher for this study is a current registered healthcare professional with the Health and Care Professions Council in the UK and has training and experience of obtaining written informed consent. With the participants consent, the researcher, working with the specialist nurse will obtain data from the participant's medical records pertaining to outcome measures (Table 1).

**Table 1. table1-02601060241307768:** Outcome measures.

Variable	Instrument/scale
Age	Age will be measured in years based on the date of birth obtained from medical records.
Sex	As recorded in medical records.
Ethnicity	As recorded in medical records.
Original domicile	Defined as own home/care home/sheltered accommodation, according to medical records.
Mobility status prior to admission	Defined as independent/independent with 1 stick/independent with 2 sticks/independent with frame/wheelchair.
Nutritional screening	Screening assessment according to the Malnutrition Universal Screening Tool (0, 1 or 2).
BMI	Calculated by ward staff; where not possible, MUAC score.
REE	Calculated according to guidance (Todorovic and Mafrici, 2018)
Smoking status	Confirmed on admission; answered as yes or no.
Alcohol	Confirmed on admission; calculated as units per week.
Fracture type	Classified as intra-capsular or extra-capsular, confirmed on admission with an x-ray performed in the emergency department.
ASA Grade	Classified following anaesthetic pre-assessment by anaesthetist (1–5).
Acute length of stay	Measured from admission to discharge from the acute ward, in days.
Discharge location	Defined as original domicile/rehabilitation unit/care home.
Past medical history	Data will be obtained from medical records regarding cardiovascular, respiratory, diabetes, cognitive decline, arthritis and history of previous fractures.

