### Data storage and analysis

Participant identifiable data (name, date of birth and hospital number) will be used to create a unique identifier that will ensure the correct food diary data is recorded against the correct patient, when accounting for a participant's potential movement between rooms during their ward stay. Once the participant's LOS and discharge destination data has been obtained, the participant's data will be anonymised and assigned a unique reference number. All participant data will be recorded and held within the trust site to maintain confidentiality and the transfer of patient information once assigned an identifier will be from the research department to the researcher's secure email.

Baseline nutritional requirements for REE, total energy expenditure (TEE), protein, carbohydrates and fat nutritional requirements per day will be calculated according to the specific guideline formula (Todorovic and Mafrici, 2018). In the instance where BMI is outside of the range 18.5 to 30 kg/m^2^, calculation adjustments will be made as per the guideline recommendations (Todorovic and Mafrici, 2018). Regarding physical activity and diet-induced thermogenesis (PAL), a combined factor range of 1.0 to 1.10 will be used, which the guidelines state is a ‘post-surgery factor’ (Todorovic and Mafrici, 2018). In cases where there is a range specified, calculations of nutritional requirements will be made at both the lower and higher scale. Demographic variables will be presented in descriptive summaries such as mean ± SD and median for continuous variables and percentages for categorical variables. For statistical analysis we will present descriptive statistics for REE met per day and to make inferences, we will take an average of the proportion of REE intake of the total food diary.

Multiple regression analysis will be used to explore if REE is a predictor of LOS, with post-operative complications and medical history used as confounders along with those who have capacity or not. Due to a small sample size, we acknowledge that caution should be taken with secondary subgroup analysis. In addition, where REE is met or exceeded, participants food diaries will be scrutinised to explore if this is attributed to a specific category of food (e.g. a high-fat dessert item) and where REE is not met, food diaries will be scrutinised to explore if this is related to complications reported.

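### The protocol sets no common window for counting complications; if checks run to discharge, time at risk grows with length of stay and biases the analyses that use complications

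*Protocol article*

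**What the plan says.** Three places in the protocol article bear on when complications are recorded.

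- **Covariates:** "the occurrence of post-operative complications will be checked daily with the gatekeeper per participant". This gives a frequency and a source, but no last day.
- **Food diary protocol:** the researcher speaks daily with the named nurse "regarding complications that may develop post-operatively during the study period". The study period is not defined for the individual participant. The diary itself "will conclude at post-operative day three inclusive".
- **Adverse events:** the participant's "end point in the study will be when LOS and discharge destination data is obtained by the researcher". This is the only statement of when a participant's time in the study ends. After certain adverse events, however, "the participant will be removed from the study, which was agreed after consultation with the study site research department".

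Table 1 (under Enrolment procedure) defines acute LOS as "Measured from admission to discharge from the acute ward, in days".

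Complications have two uses. Under Data storage and analysis, "Multiple regression analysis will be used to explore if REE is a predictor of LOS, with post-operative complications and medical history used as confounders"; I take the predictor to be the average proportion of resting energy expenditure (REE) met by intake, as the preceding paragraph there indicates. Under Research aims and Dietary intake, complications are an outcome to be related to intake.

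**The concern.** A covariate should be ascertained in the same way whatever the value of the outcome. If complications are looked for on every day until discharge, a long stay gives more days on which one can be found. Anything that lengthens the stay then raises the chance of a recorded complication, and the LOS model shows a complication effect that is partly or wholly a product of observation time.

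Two secondary results could be distorted: the intake coefficient in the LOS model, because it is adjusted for this covariate, and the intake-complication association. If low intake goes with longer stay, the latter is pushed in the direction of the second hypothesis. The primary aim, intake compared with REE needs, is not touched.

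**Working it through.** **1. Which window do the documents give?** The study period under Food diary protocol can be read in three ways.

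- *The diary, day 0 to day 3.* The sentence closes the Food diary protocol section. Everyone still in hospital then has the same window.
- *Up to the participant's end point.* Covariates sets no day-3 limit and pairs the checks with LOS, and Adverse events gives the only participant end point. Time at risk grows with LOS.
- *The calendar phase:* "The study will be conducted in one phase of 4 weeks". Ward checks are still cut off by discharge, and late enrolees are watched for less time.

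The second reading is the better supported, but it is an inference from separate sections.

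**2. Time at risk is not LOS itself.** LOS starts at admission and post-operative checks start at surgery. With an assumed 0.5-1.5 days before surgery, the observed share of an 8-day stay is 6.5/8 = 81% to 7.5/8 = 94%; of an 18-day stay it is 16.5/18 = 92% to 17.5/18 = 97%. Removal after an adverse event can end observation sooner.

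**3. Chance of a recorded complication, checks to discharge.** The documents give no complication hazard. Assume a constant hazard h = 3% per day, no effect of complications on LOS, and surgery one day after admission. Then P = 1 - (1 - h)^(LOS - 1):

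| LOS (days) | P |
|---|---|
| 6 | 1 - 0.97^5 = 14% |
| 10 | 1 - 0.97^9 = 24% |
| 15 | 1 - 0.97^14 = 35% |
| 25 | 1 - 0.97^24 = 52% |

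With a four-day window, P = 1 - 0.97^4 = 11% at every LOS.

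**4. LOS by complication status, n = 30.** The protocol gives no figure to reproduce, so this is simulation. Assumptions: lognormal LOS with median 12 days, log-SD 0.6 and minimum 5 days; time to complication geometric and independent of LOS; two-sided 5% t-test on log LOS; 3000 studies.

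| Hazard per day | False rejection, checks to discharge | Fixed days 0-3 |
|---|---|---|
| 2% | 35% | about 5% |
| 3% | 44% | about 5% |
| 5% | 55% | about 5% |

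The artefactual difference in LOS is about 6.5 days.

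**5. Sensitivity to the assumptions.**

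- Median LOS 8, 12 or 18 days, log-SD 0.4 or 0.6, minimum 6 days, hazard 2%, 5% or 10% per day, testing the correlation of complication status with log LOS: false rejection 14-61%, mean spurious correlation 0.15-0.40, difference 1.4-11.0 days. With the fixed window, false rejection is 3.5-6.6%.
- Early-loaded hazard (8% per day for four days, then 1%): about 10%.
- Calendar reading (enrolment uniform over 28 days, hazard 2-5%): 12-18%.

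**6. The planned intake analyses, checks to discharge, hazard 2-5%, LOS as in step 4.**

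- *Intake unrelated to LOS and to complications:* the adjusted intake coefficient is about 0 with 4.8-4.9% rejection; intake-complication rejection is 4.8-5.9%. Both are about nominal.
- *True intake-log LOS correlation of -0.3:* adjustment moves the coefficient from about -0.167 to between -0.153 and -0.146, an attenuation of 1 - 0.153/0.167 = 8% to 1 - 0.146/0.167 = 13%. Intake-complication false rejection is 7-9%. Allowing for stronger assumed correlations, the ranges are about 7-13% attenuation and 7-17% false rejection.
- *Intake affects complications but not LOS:* complication status depends on both intake and LOS, so adjusting for it induces a spurious coefficient of about +0.04 to +0.06 in log LOS per SD of intake. Its sign is opposite to the second hypothesis.

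**The case against.** The strongest reply is that no section says the checks run to discharge. The sentence with the named nurse stands in the food diary section, and Data storage and analysis also relates reported complications to the diaries. On that reading everyone has the same four days and the artefact vanishes. This stands as far as it goes: the harmful reading is not established. But the day-3 limit is not stated for complications either, and the other two readings both carry the bias.

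A reader might infer that surveillance time equals LOS, so that complications and LOS are associated by construction. The documents do not support that. The window is open, LOS begins before surgery, and removal can end observation before discharge.

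Three further points have weight. The 35-55% belongs to a test of LOS by complication status, whereas complications are only an adjustment term in the planned model; for the intake coefficient the effect is much smaller and, where intake truly affects LOS, towards the null. A constant hazard over a long stay drives the large figures, and an early-loaded hazard cuts them to about 10%. The analyses are secondary and exploratory, and the article advises caution over subgroup analysis and generalising; that caution concerns sample size, though, and not this bias.

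Finally, the coding of the covariate (any event, count or rate) may be left to a document not shown. That is fair, and its absence is not the complaint. The article itself states the daily checks, the end point and the covariate role, and on the better-supported reading these combine badly.

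**Conclusion.** The concern holds conditionally. The protocol fixes no common complication window. If checks run to the stated end point, time at risk rises with LOS, and recorded complications and LOS are linked without any causal effect. If checks stop at day 3, there is no problem.

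On the harmful reading, the complication-LOS association is not interpretable under the constant-hazard assumptions. The intake results are biased only modestly, and when intake is related to neither LOS nor complications their error rates stay nominal. That recorded complications rise with LOS follows from the design alone; every figure for size rests on LOS and hazard values that the documents do not give.

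**What to change.** For every analysis that relates complications to intake or LOS:

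- count complications over one fixed post-operative window common to all participants, for example diary days 0-3, or analyse them per post-operative day at risk;
- do not enter any complication before discharge as a yes/no covariate for LOS;
- report later complications descriptively.

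Also reconcile Food diary protocol with Covariates, both on the window and on the source, since one names the named nurse and the other the gatekeeper.

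Checks are already daily, so this changes analysis wording and not data collection. It has two costs. There are fewer events: with 30 patients and a four-day window, the expected number is 30 x (1 - 0.98^4) = 2.3 at an assumed hazard of 2% per day and 30 x (1 - 0.95^4) = 5.6 at 5%. And a day 0-3 window coincides with the intake measurement, so whether low intake preceded the complication or followed it stays unclear.

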### Data storage and analysis

Participant identifiable data (name, date of birth and hospital number) will be used to create a unique identifier that will ensure the correct food diary data is recorded against the correct patient, when accounting for a participant's potential movement between rooms during their ward stay. Once the participant's LOS and discharge destination data has been obtained, the participant's data will be anonymised and assigned a unique reference number. All participant data will be recorded and held within the trust site to maintain confidentiality and the transfer of patient information once assigned an identifier will be from the research department to the researcher's secure email.

Baseline nutritional requirements for REE, total energy expenditure (TEE), protein, carbohydrates and fat nutritional requirements per day will be calculated according to the specific guideline formula (Todorovic and Mafrici, 2018). In the instance where BMI is outside of the range 18.5 to 30 kg/m^2^, calculation adjustments will be made as per the guideline recommendations (Todorovic and Mafrici, 2018). Regarding physical activity and diet-induced thermogenesis (PAL), a combined factor range of 1.0 to 1.10 will be used, which the guidelines state is a ‘post-surgery factor’ (Todorovic and Mafrici, 2018). In cases where there is a range specified, calculations of nutritional requirements will be made at both the lower and higher scale. Demographic variables will be presented in descriptive summaries such as mean ± SD and median for continuous variables and percentages for categorical variables. For statistical analysis we will present descriptive statistics for REE met per day and to make inferences, we will take an average of the proportion of REE intake of the total food diary.

Multiple regression analysis will be used to explore if REE is a predictor of LOS, with post-operative complications and medical history used as confounders along with those who have capacity or not. Due to a small sample size, we acknowledge that caution should be taken with secondary subgroup analysis. In addition, where REE is met or exceeded, participants food diaries will be scrutinised to explore if this is attributed to a specific category of food (e.g. a high-fat dessert item) and where REE is not met, food diaries will be scrutinised to explore if this is related to complications reported.

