### Hypothesis

We hypothesise that older adult hip fracture patients will not be meeting their daily REE needs.We hypothesise that a reduced dietary intake due to participants being unable to meet their daily REE needs because of trauma, anaesthesia and surgery will have a negative impact on LOS and post-operative complications.We hypothesise of an association between reduced dietary intake and a combination of nausea, delirium and pain.To our knowledge, this is the first study to use a weighed food diary for older adult hip fracture patients from the day of surgery (day zero) to post-operative day three inclusive that will not require patient or ward staff recall. With data collection being conducted directly by the researcher, this will increase the accuracy of recording dietary intake.

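### The whole-diary intake average overlaps the onset of complications, so it cannot show whether low intake preceded a complication or followed it

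*Protocol article*

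**What the plan says.** Under Dietary intake, the article will "explore the effect of dietary intake as a predictor of LOS and post-operative complications". The second hypothesis points the same way: reduced intake "will have a negative impact on LOS and post-operative complications".

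The intake variable is set under Data storage and analysis. REE met per day is described, and "to make inferences, we will take an average of the proportion of REE intake of the total food diary". According to Food diary protocol, the diary "will commence on the participants day of surgery (day zero) and will conclude at post-operative day three inclusive", which makes four days.

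Complications are collected over the same days. Food diary protocol has the researcher ask the named nurse daily about "complications that may develop post-operatively during the study period, such as delirium, pressure ulcers, infection and venous thromboembolism". Covariates adds that "the occurrence of post-operative complications will be checked daily with the gatekeeper per participant".

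The third hypothesis reads: "We hypothesise of an association between reduced dietary intake and a combination of nausea, delirium and pain". Delirium is thus both a listed complication and a factor tied to reduced intake. Data storage and analysis also plans to look through diaries with unmet REE for a link to reported complications. Nothing in the article lags intake, ends the average at onset, or sets aside complications already present.

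**The concern.** A predictor should be measured before the outcome it predicts. Here the four-day mean can include days on which the patient already had the complication. A patient who becomes delirious on day 1 and then eats little will have a low average, and that low average will be read as preceding the delirium.

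If complications suppress appetite and intake has no effect on complications, patients with complications will still show lower average intake. Read in the direction of the second hypothesis, that pattern looks like support. The Discussion hopes the results will support the education and training of those who provide dietary care, so presenting a consequence of illness as a modifiable cause would matter.

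**Working it through.** The article gives no sample-size or power calculation for this question, so there is no stated figure to reproduce. Two checks apply.

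**1. Overlap, from the article alone.** The diary has four days (0, 1, 2, 3). For onset on day k, the share of averaged days on or after onset is (4 - k)/4. A fall of D points of REE from onset lowers the average by D x (4 - k)/4. D = 20 is an illustrative assumption.

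| Onset day k | Share on or after onset | Shift in average, D = 20 |
|---|---|---|
| 0 | 4/4 = 100% | 20 points |
| 1 | 3/4 = 75% | 15 points |
| 2 | 2/4 = 50% | 10 points |
| 3 | 1/4 = 25% | 5 points |

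Complications starting after day 3 have no overlap.

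**2. Consequence for a test.** The sample size of 30 is from Study sample. Every other input below is an assumption, because the article gives no complication rate, standard deviation (SD) or size of intake fall. Intake has no effect on complications in any scenario. The test is a two-sample t-test of the four-day mean by complication status, at 5%.

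*Simulation A.* Mean proportion of REE met is 0.35, 0.60, 0.70 and 0.75 on days 0 to 3; between-patient SD 0.20; within-patient SD 0.15. Complications occur in 30-50% of patients, and 50-80% of those start within days 0-3. There were 3,000 runs per scenario.

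| Scenario | Rejection at 20% fall | 35% fall | 50% fall |
|---|---|---|---|
| 50% of onsets in the diary window | 7-8% | 14-15% | 24-26% |
| 30% complications, 80% in window | 11% | 27% | 49% |
| 50% complications, 80% in window | 14% | 33% | 57% |

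The apparent deficit in patients with complications is 4-17 points of REE.

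*Simulation B.* Mean 60% of REE; between-patient SD 20 points; day-to-day SD 15 points; complications in 20-40% of patients; onset uniform over days 0-3; about 4,000 runs per scenario. The expected deficit is D x (1 + 0.75 + 0.50 + 0.25)/4 = 0.625D, which is 6.25, 12.5 and 18.75 points for D = 10, 20 and 30. The simulated deficits were about 6, 12.5 and 19 points. Rejection rates were 10-12%, 24-33% and 44-59%, against about 5% with D = 0.

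*Intake before onset only.* Simulation A, comparing mean intake up to the day before onset with the same days in patients still at risk, rejects in 4.0-5.9% of runs. Simulation B, using day-0 intake for onsets on day 1 or later, rejects in 4.5-6.0%, with a mean difference between -0.5 and +0.2 points. This return to about 5% is expected by construction, because simulated intake falls exactly at onset.

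**The case against.** The strongest reply is that much of the plan is non-directional. The Abstract speaks of a relationship and of associations, and Research aims and Discussion speak of correlation. For a correlation, the whole-diary mean is a legitimate summary. When complications lower intake the two really are associated, and the rejection rates above are then power to detect that association. They count as false positives only under the directional reading. This stands, and it confines the point to the wording in Dietary intake and the second hypothesis.

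A second reply is that no complications model is written down. The one regression set out has length of stay (LOS) as outcome and complications among the confounders. This also stands. A reader might infer that the article prescribes a comparison of the four-day mean by complication status and forbids any other intake summary. It does neither. It names one summary for inference, and applying that summary to complications is the natural reading, not a quoted instruction. A full protocol or analysis plan may supply the model, but the averaging rule itself is stated here.

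Third, the plan partly considers the reverse direction, through the third hypothesis and the inspection of diaries with unmet REE. That inspection is descriptive and does not use time order. Removal after an adverse event shortens the diary for some serious events. Its list is open-ended, but its examples are stroke, myocardial infarction and major haemorrhage, not the complications listed under Food diary protocol.

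Finally, the article urges caution because the sample is small. That addresses precision and generalisation, not the order of events.

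**Conclusion.** The point holds for the directional question. With the average taken over days 0-3 and complications arising over the same days, the named summary cannot separate low intake leading to complications from complications lowering intake. The 25-100% overlap follows from the article's own windows.

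The size of the bias is not known. The simulated range, from slightly above 5% to over 50%, rests wholly on assumed inputs. It requires that complications do reduce eating, which the third hypothesis allows for delirium. A reader might infer that the study would falsely confirm its second hypothesis in up to half of cases. The article does not support that: it gives none of the inputs, fixes no test, and frames much of the aim as correlation.

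The whole-diary average is not at fault for the question of whether REE is met. The LOS result shares part of the overlap, since a complication can both lower intake and lengthen stay. The planned adjustment for complications deals with this only in part.

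This is a secondary, exploratory objective, but the bias runs towards the stated hypothesis and can be reduced with data already planned.

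**What to change.** - Record the day of onset at the daily complication check.
- For the directional question, base inference on the mean proportion of REE met before onset of the first complication of any type. For onset on day k (k from 1 to 3), use days 0 to k - 1 and compare with the same days in participants still free of complications. For onset after day 3, use the full diary.
- Pool complication types. Separate models for each would be too sparse with 30 participants: at an assumed 30% rate there are 0.30 x 30 = 9 complications, spread over at least four types.
- Keep the whole-diary average for the REE question and for the correlation in Research aims, and label the latter a non-directional association.
- Report intake on and after onset separately, as evidence on the third hypothesis.
- State that the LOS result shares part of this overlap.

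The cost is a few lines of text and a date against checks already planned. Complications starting on day 0 drop out (about 1-2 of 9 in simulation A), day-1 onsets rely on day-0 intake alone, and intervals widen. Appetite loss before a complication is recognised would still contaminate pre-onset intake; the simulations did not test this, and it should be stated as a limitation.
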